Exclusions	Body mass index (BMI) > 35 Kg/m², advanced local disease (T4), adenocarcinomas of the transverse colon and rectum (including that of appendix, hepatic flexure, splenic flexure, overlapping sites and unspecified cancer of the colon), multiple primary colon tumors, prior history of cancer in the past 5 years. However, patients with non-melanoma skin cancer (NMSC) as well as in situ tumors (ICD-10 codes D00-D09) and benign tumors (ICD-10^a^ codes D10-D36) will not be excluded. The following patients will also be excluded: patients who underwent emergency colectomy, patients with gastrointestinal stromal tumor (GIST), neuroendocrine cancers, sarcoma cases, or patients with previous abdominal surgery. Additional excluded cases include robotic colectomies (OPS = 5–987).	Advanced local disease (T4), patients diagnosed with subtypes of colon cancer located on the appendix (C18.1), hepatic flexure (C18.3), transverse colon (C18.4), splenic flexure (C18.5), or overlapping sites of the colon (C18.8), and all unspecified sites (C18.9) – as well as cancer of the rectosigmoid junction (C19) will be excluded. Patients with prior history of cancer in the past 5 years (except NMSC, in situ tumors (ICD-10 codes D00-D09) and benign tumors (ICD-10 codes D10-D36)) will be excluded. In addition, patients with an additional GIST diagnosis, neuroendocrine cancers, sarcoma cases, patients with previous abdominal surgery for malignant indications as well as patients treated with emergency or robotic colectomy (OPS = 5–987) will also be excluded. Since data on BMI, previous surgery for non-malignant indications and CCI are not available in MV cancer registry, we will not use these covariates as exclusion criteria.
Treatment strategies	1. Laparoscopic colectomy 2. Open colectomy	Same as target trial
Grace-period for treatment implementation	–	The first three months after confirmed stages I–III colon cancer diagnosis.
Treatment assignment	Randomization, at baseline	The patient’s assignment to one of the two treatment strategies will be non-random. But randomness will be emulated by cloning patients in both arms.
Outcome	Death from all causes over a follow-up period of 60 months from baseline (start of follow-up)	Same as target trial (5 year OS)
Type of outcome	Time-to-event data	Same as target trial

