Follow-up	Follow up begins at diagnosis and the random allocation of patients to either treatment arms and then scheduled follow-up information according to German S3- guideline for colorectal cancer (German Guideline Program in Oncology 2019).	Patients will be followed from time-zero (date of diagnosis) until death from any cause, last date of information or administrative censor date (31.12.2023), whichever will come first.
Censoring	Loss to follow-up, administrative censor date (31.12.2023).	Same as target trial
Causal contrast	Intention-to-treat effect, per-protocol	Observational analogue of the per-protocol effect
Effect measure	Hazard ratio (HR), mean survival time difference	Same as target trial
Analysis plan	Multivariable Cox regression, absolute risk difference and restricted mean survival time (RMST)	Inverse-probability weighted Royston- Parmar parametric survival model. Further to the HR, absolute risk-difference, RMST difference will be calculated.
Covariate adjustments	ϖ Socio-economic characteristics: Age at colon cancer diagnosis (in years) and sex. ϖ Clinical characteristics: UICC^b^ stage (I, II or III), treating institutions, tumor laterality (left or right), treatment period (2008–2009, 2010–2014, 2015–2018), performance score (ECOG = 0, 1, or 2), hospital classification (certified colon center or not), local residual tumor margin status (yes, no, or not assessable), grade (low, intermediate or high), and number of harvested lymph nodes (< 21 or ≥ 21).	ϖ Socio-economic characteristics: same as target trial. ϖ Clinical characteristics: same as target trial.
Sensitivity analysis	Excluding cases with missing values (complete case analysis, CCA)	Sensitivity analyses: - 1) Repeat the same analysis on patients with complete case data - 2) Including all advanced local disease (stage T4N0-2M0) cases - 3) Quantitative bias analysis using the E-value method to evaluate the effect of potential residual confounders (BMI, comorbidity, previous abdominal surgery for non-malignant indications)
Comparator analysis		Comparator analyses: - Comparator 1) DAGs-guided naïve analysis of using fully adjusted cox proportional hazards model - Comparator 2) An Inverse-probability-weighted regression-adjustment (Doubly robust) analysis

^a^ ICD-10 = The International Classification of Diseases, 10th Revision

^b^ UICC = Union for International Cancer Control

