Patients will be followed up from the date of assignment to either treatment modality until death from any cause (the outcome of interest), the last date of follow-up, or the administrative censor date (31.12.2023), whichever occurs first. This administrative censor date is chosen to ensure that patients are observed for at least five years. Patient follow-up will be made in accordance with the recommendation of the German S3- guideline for colorectal cancer (German 2019). In the emulated study, we will start following the patients at time-zero, which is defined as the time point at which the eligibility criteria will be met. The initiation of treatment will have to occur within the first three months after the diagnosis of colon cancer (defined grace-period). Follow-up will end on the date of death, last date of follow-up, or 60 months after time-zero, or the administrative censor date Dec. 31, 2023, whichever will occur first. The main outcome will be 5-year OS, which refers to the duration from time-zero until death from any cause. The estimated hazard ratio will be complemented by the mean survival difference (at 1, 3, and 5 years) between the patients treated with laparoscopic and open surgery, respectively. Since our study covers a long period of time (2008 to 2018), treatment period-specific analyses will be performed to mitigate potential bias that may be induced by changes in clinical knowledge and practice over time (Hou et al. 2022).

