#### Statistical analysis

Patient characteristics will be summarized using frequencies and percentages for categorical variables, whereas means and standard deviations or medians and interquartile ranges will be used for continuous variables, depending on their distributions.

We will use the clone-censor-weight design to emulate the hypothetical target trial (Hernan and Robins 2016). Since each patient will be eligible for one of the two surgical treatment modalities during the three-month grace-period, we will first clone (copy) each patient record, and each clone will then be allowed to enter both treatment arms for the duration of the grace-period regardless of the surgical modality they will actually receive later. This will emulate randomization in the specified target trial and addresses the issue of confounding at baseline, as both treatment arms are identical in terms of baseline patient characteristics. Cloning also offers the opportunity for even distribution of survival times (before surgery, for the entire grace-period or any early deaths that may occur before treatment) between the two surgical treatment modalities, allowing us to circumvent the problem of immortal time bias (Hernan and Robins 2016). In the next step, we will censor clones over time if non-compliance with the initially assigned treatment strategy is detected from that timepoint onward. This implies that we will censor clones assigned to laparoscopic colectomy (including converted colectomy) but whose records indicate that they underwent open colectomy within the grace-period, or vice versa. The censoring times will be defined corresponding to the time of each censoring event and will be incorporated into the weighting model described below. Figure2 provides all possible treatment paths and the respective censoring mechanism of the trial emulation for both treatment and outcome models.

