Finally, we will use an inverse-probability weighted Royston-Parmar parametric survival model (RPpsm) to estimate an unbiased causal effect of laparoscopic versus open surgical treatment on OS via hazard ratio. If incorporating the final weight (derived from IPTW and IPCW) into the RPpsm will not be achieved, we will alternatively use weighted pooled logistic regression to model the outcome. When the event of interest (death from any cause) occurs, that event is considered to be an event solely in the patients’ originally planned treatment arm, in which each patient is initially consistent and remains uncensored at the point in time when the event occurs. On the other hand, the cloned records will be censored at that exact time the event occurs, which is accomplished by censoring indicators. Using weighted RPpsm postestimation tools, OS will be estimated using differences in absolute risk and restricted median survival (RMST) at 1-, 3-, and 5-years and up to 1-, 3-, and 5-years, respectively. To account for the weighting to be applied, point estimates will be accompanied by 95% confidence intervals via non-parametric bootstrapping with 500 replicates. A weighted Kaplan-Meier method will be used to compare time-to-event curves over a 60-months period according to surgical treatment modality. We will compare our results with estimates from the literature. We make use of the CERBOT (Comparative Effectiveness Research Based on Observational Data to Emulate a Target Trial) tool (see Additional file 1) in our emulation process (Zhang et al. 2024).

It is crucial to handle missing data properly to obtain more powerful models resulting in better estimates (Mbona et al. 2023). We will use multiple imputation via the chained equations method to impute missing values in covariates, assuming that observed missing values are missing at random (White and Royston 2009). In the literature, this method is also referred to as “multivariate imputation with sequential regression” and “imputation using fully conditional specifications” (Raghunathan et al. 2001; van Buuren et al. 1999). All variables of the analysis dataset, including the outcome variable, will be used for the imputation model and ten datasets (m = 10) will be imputed.

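### The outcome model reports one hazard ratio and takes the 1-, 3- and 5-year risk and RMST differences from the same fit, without saying that the arm effect may vary with time

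*Protocol article*

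**What the plan says.** **Outcome model (Statistical analysis).** The final step is specified as follows: "inverse-probability weighted Royston-Parmar parametric survival model (RPpsm) to estimate an unbiased causal effect of laparoscopic versus open surgical treatment on OS via hazard ratio". Pooled logistic regression with the same weights is the fallback.

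**One hazard ratio, plus time-specific measures (Design of the target trial and the emulated trial).** "The estimated hazard ratio will be complemented by the mean survival difference (at 1, 3, and 5 years"). Table 1 likewise lists the HR and a mean survival time difference as effect measures.

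**Same fit for the absolute measures (Statistical analysis).** "Using weighted RPpsm postestimation tools, OS will be estimated using differences in absolute risk and restricted median survival (RMST) at 1-, 3-, and 5-years". Weighted Kaplan-Meier curves over 60 months are also planned, to compare the arms.

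**Time zero and grace period (Table 1).** "Patients will be followed from time-zero (date of diagnosis) until death from any cause"; the grace period is "The first three months after confirmed stages I–III colon cancer diagnosis".

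**Cloning (Statistical analysis).** "each clone will then be allowed to enter both treatment arms for the duration of the grace-period". The stated purpose is that pre-surgery survival time and early deaths fall evenly on both arms.

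The article mentions neither a treatment-by-time term nor a check of proportionality.

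**The concern.** By the design's own logic the two arms hold the same patients until surgery, so the HR is 1 over that stretch whatever surgery does afterwards. If surgery type has an effect, the HR therefore changes during follow-up. A model with one constant arm coefficient would be misspecified, and its estimate would be an average over follow-up that depends on when the deaths occur. Describing that number as an unbiased causal effect claims too much.

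The practical stake lies in the absolute measures. They were added to complement the HR. If they are predicted from a model with a constant HR, they inherit its constraint: an effect concentrated soon after surgery is spread over five years, and the 1- and 3-year results are the ones that suffer.

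**Working it through.** The article gives no survival, event or effect figures, so there is nothing of its own to reproduce. The check asks what a constant-HR fit would return in large samples if the truth were not proportional. All survival inputs below are assumptions. Risk differences are laparoscopic minus open; RMST differences are gains with laparoscopy.

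**Method.** Take two equal weighted arms with true survival S_L and S_O and death densities f_L and f_O. A proportional-hazards model with a free baseline (close to a flexible Royston-Parmar fit on the hazard scale) converges to the θ that solves

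∫ [ f_L − (f_L + f_O) · θS_L / (θS_L + S_O) ] dt = 0,

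with baseline Λ(t) = ∫₀ᵗ (f_L + f_O) / (θS_L + S_O) du. Fitted survival is exp(−Λ) for open and exp(−θΛ) for laparoscopic. Risk and RMST differences from these curves are compared with the true ones.

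**Check 1: only the shared pre-surgery hazard.** From the article: time zero at diagnosis, surgery within 3 months, 60-month horizon. Assumed: open-arm 5-year survival 60–80%; HR after surgery 0.7–0.9; exponential surgery times truncated at 3 months, with rate ln2/0.5 or ln2/1.0 per month.

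- The fitted HR differs from the post-surgery HR by at most 0.006.
- The 1-year risk difference is overstated by about 5–9% relative (at most about 0.2 points), the 3-year one by about 1%. The 5-year one is within 0.5%.
- Example (5-year survival 70%, post-surgery HR 0.8, slower timing): fitted HR 0.804; 1-year −1.32 versus true −1.22 points; 3-year −3.46 versus −3.43; 5-year −5.07 versus −5.09.
- Extreme case, all surgery at month 3, same example: 1-year −1.28 versus −1.00 points, 3-year −3.33 versus −3.23.

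**Check 2: a difference in early operative mortality.** Assumed: a 0.08-year wait without deaths; a 0.25-year perioperative phase with mortality 2% (laparoscopic) versus 3% or 4% (open); then 0.055 deaths per year in both arms.

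True values for 2% versus 4% can be checked by hand. At 1 year, 0.67 year of late hazard has elapsed: (0.04 − 0.02) × exp(−0.055 × 0.67) = 0.02 × 0.964 = 1.93 points. At 5 years, 0.02 × exp(−0.055 × 4.67) = 0.02 × 0.773 = 1.55 points.

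| Measure | 2% v 4%: true | fitted | 2% v 3%: true | fitted |
|---|---|---|---|---|
| HR | not constant | 0.92 | not constant | 0.96 |
| Risk difference, 1 y (points) | −1.93 | −0.51 | −0.96 | −0.24 |
| Risk difference, 3 y | −1.73 | −1.21 | −0.86 | −0.60 |
| Risk difference, 5 y | −1.55 | −1.75 | −0.77 | −0.88 |
| RMST gain, 1 y (days) | 5.7 | 1.0 | 2.9 | 0.5 |
| RMST gain, 3 y | 19.1 | 7.4 | 9.5 | 3.6 |
| RMST gain, 5 y | 31.0 | 18.3 | 15.5 | 9.0 |

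**Which mechanism drives check 2?** Removing the wait altogether in the 2% versus 4% case changes the fitted HR only from 0.922 to 0.923 and the fitted 1-year risk difference from −0.51 to −0.54 points. The distortion comes from the early mortality difference. The shared pre-surgery period, taken alone, errs in the opposite direction (check 1).

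**The case against.** **The article never says proportional hazards.** A reader might infer that a constant HR has been prescribed and that the model is therefore wrong by design. The text does not go that far. Royston-Parmar models can carry time-dependent effects, and an article may leave scale, knots and interaction terms to a fuller plan. This stands: the constant effect is an inference from a single reported HR. What remains is that the article fixes one HR as the causal estimate, takes the absolute measures from the same fit, and is silent on variation with time in a design that guarantees such variation if there is an effect.

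**The shared grace period barely matters.** A reader might also infer that it distorts the 1- and 3-year results by itself. Check 1 does not support this, except modestly at 1 year if nearly all operations came late in the grace period. Moreover, the article has a death counted in one arm only, with the other clone censored, so pre-surgery hazards in the analysed data may not be shared at all. That conflict with the stated purpose of cloning is a separate matter.

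**The larger distortion rests on an assumption.** The article gives no operative mortality and does not say that any difference is concentrated early. This stands too, so the figures in check 2 show sensitivity and are not predictions. A harsher construction, adding a 9% higher late hazard after laparoscopy (0.060 versus 0.055 per year), brings the fitted HR to 1.00 and the fitted 5-year RMST gain to 0.4 days against a true 14.7. That late hazard is chosen to cancel the early benefit, and nothing in the article points to it.

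**Safeguards exist.** Weighted Kaplan-Meier curves would reveal early separation or crossing, and the plan does not rely on the HR alone. But the reported differences come from the model, and no rule says what happens if the curves disagree with it.

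**Conclusion.** The point holds as a gap in specification with a cheap remedy. With time zero at diagnosis and cloning until surgery, hazards cannot be proportional from time zero unless there is no effect, so a single HR can only be an average over follow-up.

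The size depends on the cause. The shared pre-surgery period alone is minor when surgery is spread over the grace period. An early operative mortality difference of 1–2 points would leave a constant-HR fit showing only about a quarter of the true 1-year risk difference (0.24/0.96 = 25%; 0.51/1.93 = 26%) and about 60% of the 5-year RMST gain (9.0/15.5 = 58%; 18.3/31.0 = 59%). The 5-year risk difference, which is closest to the research question, would be off by only 0.1–0.2 points, so the 5-year survival comparison as such is not undermined.

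These magnitudes rest on assumed survival, effect and surgery timing, and on the fitted model having no time-dependent arm term.

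**What to change.** In the outcome-model paragraph of Statistical analysis:

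1. State that the weighted Royston-Parmar model includes a time-dependent arm effect, for example a spline interaction of arm with time, and that the pooled logistic fallback includes arm-by-time terms.
2. Derive the 1-, 3- and 5-year risk and RMST differences from that model and check them against the weighted Kaplan-Meier curves.
3. Describe any single HR as an average over follow-up and drop the claim that it is the unbiased causal effect.
4. Clerical: the same paragraph expands RMST with median where Table 1 and the abbreviations list have mean. Correct it to mean.

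The cost is a few extra parameters, slightly wider intervals and some wording. Fixing the time-dependent term now also avoids choosing it after the curves have been seen. Whether the risk and RMST differences should lead the report in place of the HR is a matter of preference and is not required by this point.

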**Fig. 2 Fig2:**
[figure not shown]
Definition of outcome and survival times for each patient in each emulation arm

The informative censoring (and hence associated selection bias) induced by the implementation of artificial censoring will be adjusted via inverse-probability censoring weighting (IPCW). This will reflect the likelihood of being compliant (uncensored) with the assigned treatment strategy given the confounding factors. However, prior to cloning, an inverse-probability of treatment weighting (IPTW) on the uncloned (original) population will be estimated with the aim of assigning larger weights to patients who will be less likely to undergo laparoscopic colectomy, given the individual constellation of confounding factors. These weights (IPTW and IPCW) will be estimated by running separate models using a logit function and later combined by multiplying both weights. This single combined weight will later allow us to determine an unbiased causal effect of laparoscopic versus open surgical treatment. We will then use absolute standardized differences within ≤ 10% as an indicator of adequate balance of the covariates (confounders) between the two treatment arms. If there will be evidence of imbalance, the weights at the 1st and 99th percentiles will be trimmed to reduce the effect of extreme weights. This will be achieved by replacing all weight values that are below the 1st percentile with the 1st percentile value and by replacing all weight values above the 99th percentile with the 99th percentile value.

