In the web-based DAGitty environment (https://www.dagitty.net/), we will utilize directed acyclic graphs (DAGs) to determine the minimum necessary adjustment sets of confounders to control for within the comparative multivariable model. This approach mitigates the risk of bias that may arise from conditioning on intermediate covariates or colliders and mediators (Textor et al. 2011; Tonnies et al. 2022). The causal diagram for the comparative multivariable Cox model is complemented by a literature review and discussion to identify confounders, colliders, mediators and prognostic factors (Austin and Stuart 2015; Lederer et al. 2019). By adjusting the minimum sufficient adjustment sets of confounders in our comparative model, we will be able to block any backdoor bias paths (remove relevant confounding) when estimating the total causal effect of surgical treatment modality on all-cause mortality.

We will consider the following baseline characteristics (measured before or at time-zero) as potential confounders: Age at colon cancer diagnosis, sex, year of surgical treatment (classified according to the implementation and update series of the German S3- guideline for colorectal cancer (German Guideline Program in Oncology 2019) as 2008–2009 [pre-implementation], 2010–2014 [first update], or 2015–2018 [second update]), tumor laterality (right-sided [caecum and ascending colon] tumor or left-sided [descending and sigmoid colon] tumor), hospital type (classified as either a registered colorectal cancer center or other group), performance status (ECOG ≤ 2 or Karnofsky performance status score ≥ 50%), and histologic grade (low, intermediate or high), UICC stage (I, II or III), and local tumor size (T-stage). In addition, we will adjust the following two variables that serve as quality indicators of performed surgical procedure: minimum number of harvested lymph nodes (classified as < 21 or ≥ 21) (Choi et al. 2010), and local residual tumor status within 3 months of diagnosis (no (R0), yes (R1 + R2), not assessable or missing). We will also extract the following dates accurate to the month (date of birth, diagnosis, surgery, death, neo/adjuvant therapy initiation, and conversion to open surgery) and other covariates (project specific pseudonym, tumor IDs, cause of death).

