#### Sensitivity and comparator analyses

The cancer registry does not collect data on BMI, CCI, or history of previous surgery for non-malignant indications. Given that we will be unable to emulate these potential factors, residual confounding arising from these factors is a major limitation of this study. Thus, we will perform sensitivity analyses.Of residual confounding using the E-value method (VanderWeele and Ding 2017) to provide a quantitative bias analysis for potential residual confounders (BMI, comorbidity, and previous abdominal surgery for non-malignant indications), and.After excluding patients with missing data to further evaluate the potential for selection bias that would otherwise have occurred if such cases were excluded. Further sensitivity analysis will be performed by including all patients with advanced local disease (stage T4N0-2M0).

In addition, a comparative analysis of the same but unemulated study population that started treatment at any point in time will be performed via classical Cox regression to assess the influence of our emulation process. As identified by the DAGs, the treatment effect, which adjusts for “age, grade, performance status, and tumor laterality” in this comparative model will be unbiased. Through this, we will practically examine whether the conclusion of the comparative analysis actually differs from that of the emulated study (see Additional file 2). Another comparative analysis of the same emulated population will be performed via the inverse-probability weighted regression adjustment (doubly robust) method. This approach combines the outcome modeling strategy of regression adjustment and the treatment modeling strategy of inverse-probability weighting (Smith et al. 2022). It is referred to as “doubly robust” because although it requires running two models, of which only one—the treatment or outcome model—needs to be correctly specified to obtain an unbiased estimate of the treatment effect (Smith et al. 2022).

All our analyses will be performed in STATA (version 18.0, College Station, TX: StataCorp LLC), and statistically significant associations will be declared at a p-value of less than 0.05.

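### The censoring weights name no time-updated covariate, and therapy started between diagnosis and colectomy, whose start date is extracted, is not adjusted for, excluded or examined

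*Protocol article*

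**What the plan says.** Table 1 of the protocol article starts the clock at diagnosis: "Patients will be followed from time-zero (date of diagnosis) until death from any cause". The grace period for the operation is "The first three months after confirmed stages I–III colon cancer diagnosis".

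The Statistical analysis section clones each patient into both arms and censors a clone when the operation received departs from its arm. It corrects for this with the IPCW, described as follows: "This will reflect the likelihood of being compliant (uncensored) with the assigned treatment strategy given the confounding factors". Those factors are introduced in the same section with "We will consider the following baseline characteristics (measured before or at time-zero) as potential confounders". The list is age, sex, year of surgery, laterality, hospital type, performance status, grade, UICC stage and T-stage. Two more variables follow, number of harvested lymph nodes and residual tumour status, under the sentence "In addition, we will adjust the following two variables that serve as quality indicators of performed surgical procedure". Table 1 gives a similar list and adds the treating institution.

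Pre-operative therapy appears only among dates to be extracted to the nearest month: "date of birth, diagnosis, surgery, death, neo/adjuvant therapy initiation, and conversion to open surgery". No analytic use is stated for it. It is not in the eligibility or exclusion rows of Table 1, nor part of either treatment strategy. The Sensitivity and comparator analyses section covers complete cases, the addition of T4N0-2M0 patients, and an E-value analysis that names BMI, comorbidity and previous abdominal surgery.

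**The concern.** In a clone-censor-weight analysis, cloning makes the arms identical at time-zero only. From then on, comparability depends on the censoring weights. A clone is censored when the other operation is performed, so the weights must condition on whatever is known up to that moment and predicts both the operation and death. Characteristics fixed at diagnosis cannot fully stand in for an event that happens afterwards.

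Therapy started between diagnosis and colectomy falls in exactly this window. As written, patients operated on directly and patients operated on after such therapy are mixed in both arms, and nothing in the named weight model tells them apart. If pre-treated patients more often had open surgery and also had a worse prognosis, the remaining imbalance would favour laparoscopy.

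The article calls the weighted estimate unbiased, and the residual confounding it acknowledges comes from variables the registry does not hold. Here the date is in the extract, so this gap can be closed.

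**Working it through.** The article gives no sample size, event count or therapy frequency for this point, so there is no stated figure to reproduce. The check has two parts.

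**1. Where pre-operative therapy is handled**

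| Place in the article | Treatment of pre-operative therapy |
|---|---|
| Table 1, eligibility and exclusions; the text on target trial criteria | not a criterion |
| Table 1, treatment strategies | not mentioned |
| Table 1, covariate adjustments | not listed |
| Statistical analysis, confounders and quality indicators | not listed |
| Statistical analysis, description of the weights | no time-updated covariate named |
| Statistical analysis, extracted dates | start date, combined with adjuvant therapy, to the month |
| Sensitivity and comparator analyses | not mentioned |

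The variable is available but has no role in the analysis.

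**2. Possible size, for scale only**

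All inputs here are assumptions; none comes from the article. Take a true hazard ratio of 1.00 and half of the patients operated on laparoscopically. Let pL and pO be the shares pre-treated among laparoscopic and open patients, and h the hazard ratio for death linked to pre-treatment after adjustment for the listed covariates. The apparent hazard ratio is approximately

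[1 + pL(h − 1)] / [1 + pO(h − 1)].

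For a given overall prevalence and an odds ratio (OR) linking pre-treatment to open surgery, pL and pO solve pL + pO = 2 × prevalence and pO/(1 − pO) = OR × pL/(1 − pL).

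- Prevalence 5%, OR 3: pL = 0.026, pO = 0.074. With h = 1.5: 1.013/1.037 = 0.98. With h = 2.0: 1.026/1.074 = 0.96.
- Prevalence 2%, OR 2: pL = 0.0135, pO = 0.0265. With h = 1.5: 1.00675/1.01325 = 0.99.
- Prevalence 15%, OR 3, as a supposition for T4 patients alone: pL = 0.084, pO = 0.216. With h = 2.0: 1.084/1.216 = 0.89.

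Setting the two shares directly shows how far the result depends on them:

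| pL | pO | h = 1.5 | h = 2 | h = 3 |
|---|---|---|---|---|
| 1% | 3% | 0.99 | 0.98 | 0.96 |
| 2% | 10% | 0.96 | 0.93 | 0.87 |
| 5% | 15% | 0.95 | 0.91 | 0.85 |

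The distortion is negligible if pre-operative therapy is rare. It becomes material only if such therapy is fairly common and unevenly spread between the operations.

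**The case against.** A reader might infer from the quoted sentence that the weights use nothing later than time-zero. The article does not support that. The same paragraph includes year of surgery, lymph-node count and residual tumour status, all of which are fixed only at or after the operation. The time-zero label is therefore inconsistent with the list beneath it. The narrower point stands: variables from the operation are admitted, while one that precedes it is left out.

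A reader might also infer that a known confounder is left unadjusted. The article does not say how often pre-operative therapy is given in this population, that it influences the choice of operation, or that it predicts death. It does not say that such therapy is commoner in T4 disease either. The concern is conditional on these.

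Several features limit its size. T4 disease is outside the main analysis and surgery must fall within 90 days of diagnosis, which may keep the number affected low. Stage, T-stage, grade, performance status and hospital type are adjusted for; if the assumed associations are not conditional on these, the illustration overstates the bias. The 0.89 is not a result the plan would report, because T4 patients are to be added to the main population and not analysed alone. In the pooled analysis the figure is diluted.

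The E-value is generic and indicates how strong any omitted factor would have to be. That is some protection, but a weak substitute for using a variable that is in the dataset.

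Finally, this is a condensed article with additional files not shown, and weight-model detail may be given elsewhere. That has some force for model form. It has less for the choice of covariates, because the article itemises them twice and places this date outside both lists.

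**Conclusion.** The point holds in a limited, conditional form. The plan names no time-updated covariate for the IPCW, and therapy started between diagnosis and colectomy is not adjusted for, excluded or specifically examined, although its start date is extracted. If it predicts both the operation and death, the censoring weights leave that selection in the contrast.

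Under the 2% to 5% prevalence scenarios, the main hazard ratio shifts from 1.00 to between about 0.96 and 0.99. The shift may be larger once T4 patients are added. Size and direction both rest on assumed prevalence and associations. Confidence that the bias is material is low; this is a worthwhile improvement, not a flaw that undermines the main analysis.

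**What to change.** In the Statistical analysis section, both where the weights are described and where the confounders are listed:

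- Derive pre-operative therapy (yes/no) by comparing the month of therapy start with the month of surgery, and state a rule for cases where the two coincide.
- Include it as a time-updated covariate over the grace period in the IPCW, in the main analysis and in the analysis that adds T4 patients.
- Add a sensitivity analysis without pre-treated patients. This also covers the case where the covariate is too rare for stable weights. Because it selects on an event after time-zero, it should stay a sensitivity analysis.
- Report the frequency of pre-operative therapy by operation received, so that readers can judge whether the issue matters.
- State that therapy started after the colectomy is not adjusted for, in line with the total effect the article sets out to estimate.

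The cost is one derived variable, one additional analysis and a few sentences; no new data are needed. The downsides are slightly more variable weights and some misclassification, because the therapy field combines neoadjuvant and adjuvant treatment and the dates are accurate only to the month.
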